#### Analysis of implementation

##### Outcomes

Table 3 provides the implementation outcomes and related measures for evaluating the implementation of the program. Implementation outcomes include acceptability, appropriateness, adoption, feasibility, fidelity, reach (coverage), maintenance (sustainability), and cost. Acceptability will be assessed using the enrollment, attrition, and engagement rates (percentage of study participants receiving at least one home visit and attending at least one group session), and dose. Targets have been set for each of these measures based on the medical literature and/or our pilot study results [43], and observed values from the RCT will be compared to the targets. The following targets have been set for the RCT: enrollment rate of >50%, attrition rate of <20%, engagement rate for home visits >90% and group sessions >75%, and a median dose of three or more in-home visits and attendance at group sessions.

**Table 3 Tab3:** Implementation outcomes – Measures and method of analysis

Implementation outcomes		
Outcome	Outcome measure(s)	Methods of analysis
*Acceptability*: a willingness to receive the offered intervention	- Enrollment rate (%) - Attrition/retention rate (%) - Engagement rate (% at least 1 home visit and 1 group session) - Dose of the intervention (number of visits and/or group sessions attended)	- Compare observed rates to targets set for study - Characteristics of consenters versus nonconsenters - Descriptive statistics for total dose, number of visits, number of group sessions
*Appropriateness:* from the perspective of interventionists	- Perceived benefit to participants - Convenience of implementation	Qualitative descriptive analysis of focus group and outreach meetings
*Adoption:* the intervention is appealing to providers and realistic to implement in practice	- Enrollment rate (%) - Attrition/retention rate (%) - Engagement rate (% at least 1 home visit and 1 group session) - Dose of the intervention (number of visits and/or group sessions attended)	- Compare observed rates to targets set for study - Characteristics of consenters versus nonconsenters - Descriptive statistics for total dose, number of visits, number of group sessions
*Feasibility*: the capability to carry out intervention activities	- Training of the interventionists - Delivery of the program - Perceptions of barriers and facilitators	- Evaluation of training materials, log sheets - Qualitative descriptive method to analyze focus group content
*Fidelity*: adherence to intervention components	Refer to Fidelity Checklist (Additional file 3)	- Review records of attendance at training session and monthly meetings with researchers - Review home visit records and log sheets to assess delivery of the program as planned
*Reach*: degree to which the target population is eligible to receive the intervention (coverage)	- Proportion of clients eligible - Reasons for exclusion - Characteristics of eligible clients	- Descriptive statistics
*Maintenance*: the extent to which the intervention can be sustained	- Engagement rate (%) - Attrition /retention (%) - Reported reasons for attrition - Prospects for the program’s uptake in practice setting	- Descriptive statistics - Qualitative descriptive method to analyze focus group content
*Cost*: from a societal perspective	- Health and Social Services Utilization Inventory (HSSUI) [90]	- Comparison of baseline (*T* _1_) and 6-month (*T* _2_) median costs using Mann-Whitney *U* test

Appropriateness and feasibility will be evaluated based on the results of the monthly outreach meetings and focus group sessions with interventionists. These meetings and focus group sessions will provide information on the perceived impact, and barriers and facilitators to implementation of the program. Questions asked during the focus group session will be guided by the CFIR [47] framework which facilitates the systematic exploration of the appropriateness and feasibility of the program in terms of barriers and facilitators. CFIR focuses on examining the following key domains: intervention characteristics (e.g., complexity of intervention, perception of benefits and relative advantage compared to usual practice), outer setting (e.g., credibility of intervention by provider and senior administrative agents), inner setting (e.g., team characteristics and engagement, level of coordination and collaboration, involvement of clients and caregivers, compatibility with existing systems and resources), and individuals (e.g., enthusiasm and support for intervention, consistent tracking of activities, reporting and resolving challenges, robust referrals).

Costing will assume a societal perspective [89], which implies collecting all costs, regardless of who bears them. The wider the perspective taken, the more applicable the study is to social-policy decisions. The costs of use of all types of health services from baseline to 6 months in T2DM clients and their family caregivers will be determined using the Health and Social Services Utilization Inventory (HSSUI) [90]. The HSSUI consists of questions about the respondent’s use of the following direct health care services: (1) primary care, (2) emergency department and specialists, (3) hospital days, (4) other health and community support services, and (5) prescription medications. Services specific to the program will be captured such as interventionist training, delivery of services in group sessions and in-home visits, and attendance at case conferences and outreach visits. Inquiries are restricted to the reliable duration of recall: 6 months for remembering a hospitalization and a visit to the physician, and 2 days for use of a medication. The HSSUI builds on the work of Browne et al. [91, 92] whose work was tested and assessed for reliability and validity and was acknowledged as one of the few published measures of ambulatory utilization that is empirically validated [93]. The 6-month cost data will be derived from “quantity” data for the services identified in the HSSUI and current “price” data for each service [90]. Services include: physician costs, home care services, outpatient costs, X-rays, other health care providers, emergency services, medication costs, tests, emergency room and hospitalization, and caregiver support services [90]. The product of the number of units of service (quantity) and unit cost (price) is total cost.

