Figure 2 provides the overall evaluation framework for the trial. The evaluation of effectiveness and implementation outcomes, while discussed separately below, will occur simultaneously, receive equal emphasis, and are recognized as often dependent on each other (e.g., the effectiveness of the intervention will depend on the quality and success of the implementation strategy and process). Our approach of assigning equal weight to the effectiveness and implementation components of the study is consistent with a type-2 hybrid trial [42]. Implementation outcomes examined in the trial are guided by two published frameworks: the broad implementation research framework by Peters et al. [46] and the Consolidated Framework for Implementation Research (CFIR) for systematically identifying contextual factors that can impact intervention implementation, adoption and maintenance by Damschroder et al. [47]. The Peters et al. [46] framework recognizes a range of implementation outcomes including: acceptability, adoption, appropriateness, feasibility, fidelity, cost, coverage, and sustainability. The CFIR provides a focused set of constructs to evaluate barriers and facilitators including characteristics of the intervention, outer and inner setting, individuals delivering the intervention, and the implementation process. We have developed research questions and quantitative measures and/or qualitative inquiries corresponding to each implementation outcome from these two frameworks.

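### Table 3 gives Adoption the same measures and analyses as Acceptability, so the provider-facing outcome can only repeat the client-facing one

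*Protocol article*

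**What the plan says.** The Outcomes section under Analysis of implementation names eight implementation outcomes, and Table 3 gives each one a definition, measures and analyses. Acceptability is "a willingness to receive the offered intervention". Adoption is that "the intervention is appealing to providers and realistic to implement in practice".

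The two rows carry the same measures cell: enrollment rate, attrition or retention rate, then "Engagement rate (% at least 1 home visit and 1 group session) - Dose of the intervention (number of visits and/or group sessions attended" (bracket closing there). They also carry the same analysis cell: "Compare observed rates to targets set for study - Characteristics of consenters versus nonconsenters", followed by descriptive statistics for dose, visits and sessions.

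The text around the table ties these rates to one outcome only: "Acceptability will be assessed using the enrollment, attrition, and engagement rates", with dose added and a target for each. Engagement is counted per client, as the "percentage of study participants receiving at least one home visit and attending at least one group session".

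Methods/design stresses the standing of the implementation side. "Our approach of assigning equal weight to the effectiveness and implementation components of the study" is presented there as what makes this a type-2 hybrid trial. The same section says that questions and measures or inquiries were developed for each implementation outcome.

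**The concern.** Acceptability and Adoption have different subjects. The first asks whether clients are willing to receive the program. The second asks whether providers find it attractive and workable. If both are judged on the same rates against the same targets, they cannot disagree, and the second adds nothing to the first.

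A report that follows the table would present a client result under a provider label. If clients turned down group sessions, missing the group-session target would read as weak provider adoption. If clients attended well, meeting it would read as provider appeal, whatever the staff thought. This matters because the Discussion expects adoption and implementation to be potentially high, and the row as written could not test the appeal part of that expectation.

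**Working it through.** No arithmetic beyond counting applies. The check sets the rows side by side and then looks for a provider measure elsewhere in the article.

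**Step 1: the two rows of Table 3.**

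| | Acceptability | Adoption |
|---|---|---|
| Construct | willingness to receive | appeal to providers; realistic to implement |
| Measures | enrollment, attrition/retention, engagement, dose | the same four |
| Analyses | rates against targets; consenters versus nonconsenters; dose descriptives | the same three |

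Measures shared: 4 of 4. Analyses shared: 3 of 3. Measures specific to Adoption: 4 − 4 = 0.

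**Step 2: what each measure can say about providers.**

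- *Enrollment.* Consent and baseline assessment come before randomization (Randomization design), so enrollment is settled before the program is delivered to that client. In Ontario, center staff identify and phone candidates (Screening for eligibility and enrolment). The rate therefore reflects some staff effort, but in recruiting for the study rather than in taking up the program.
- *Attrition.* The denominator of the under-20% target is not stated. If it covers both arms, then with 1:1 allocation about half of those counted have no contact with the program providers, who do not treat control participants (Program).
- *Engagement and dose.* These need a nurse, dietitian or program coordinator to deliver something, and a client to accept it. The Program section lets clients decline visits or sessions. The two measures therefore bear on realistic implementation, but they mix staff delivery with client choice.
- *Appeal to providers.* None of the four measures it.

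**Step 3: whether the row could separate the two constructs.** Take a site where staff find the program burdensome but deliver it, and clients attend. The targets can all be met. Now take a site where staff are keen but many clients decline group sessions, so that group engagement falls below its 75% target. In both cases Adoption and Acceptability receive the same verdict, and in neither does that verdict record what the staff thought.

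**Step 4: where provider information is assigned.**

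| Provider information | Assigned to |
|---|---|
| Perceived benefit, convenience (focus groups, outreach meetings) | Appropriateness |
| Training, delivery, barriers and facilitators | Feasibility |
| "Review records of attendance at training session and monthly meetings with researchers" | Fidelity |
| Prospects for uptake in the practice setting (focus groups) | Maintenance |
| Interventionists' intentions (Discussion) | Sustainability |

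The focus-group guide covers staff enthusiasm and support, relative advantage over usual practice, and compatibility with existing systems, but the text links it to Appropriateness and Feasibility. The Implementation analyses section connects the client rates to acceptability, says many also serve maintenance, and does not mention Adoption. Nowhere is a provider measure assigned to Adoption.

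**The case against.** The strongest reply has four parts.

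*Staff must deliver for clients to take up.* A reader might infer that high client uptake could be reported as adoption even though staff had not taken up the program. The documents do not support that. Home visits are made by the nurse and dietitian, and the coordinator belongs to the delivery team, so substantial engagement and dose imply substantial delivery. It would also be too strong to say that the measures carry no provider information. This part stands. What remains is that delivering a program is not the same as finding it appealing, and that a low value cannot be traced to staff or to clients.

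*Provider views are collected.* A reader might infer that the trial cannot answer the adoption question at all. That also goes too far. The focus groups and outreach meetings address it, and the Maintenance row includes prospects for uptake. The failure is in the link from those data to Adoption.

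*It looks like a copying slip in a minor, descriptive row.* The word-for-word repetition suggests this, but the article does not show what was intended, and an analyst following Table 3 would carry the slip into the report. It is fair that equal weight attaches to the implementation component as a whole and not to each row.

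*Any repair borrows from other rows.* This is true. Training and meeting attendance already serves Fidelity, and the interview themes already serve Appropriateness and Feasibility. It is a reason to let themes on appeal and realism lead, and not to build Adoption on attendance counts. Nor is 21 a secure provider denominator. It is the anticipated number of Team Climate Inventory assessments (3 roles × 7 sites), and the Program section allows further professionals on the teams.

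**Conclusion.** The point holds as a defect of one row. As Table 3 stands, Adoption duplicates Acceptability in all four measures and all three analyses. The appeal half of its definition has no measure, and the realism half is reached only through two mixed indicators.

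The size is limited. One of eight implementation outcomes is affected. That outcome is descriptive, and the PCS-12 analysis, the sample size and the secondary effectiveness outcomes do not depend on it. Reuse of client rates under Maintenance is not part of the problem, because the text states it openly and that row adds provider-relevant content.

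The conclusion assumes that Table 3 will be followed as printed. It is worth correcting before the implementation results are written, because the plan otherwise fixes an answer to a provider question that uses no provider views.

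**What to change.** Rewrite the Adoption row of Table 3 and add a matching sentence to Implementation analyses:

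1. Make the planned interventionist focus-group and outreach-meeting themes on appeal and realism the lead measure, using the qualitative descriptive analysis already specified.
2. Supplement it with a descriptive site-level tabulation of program delivery by provider role, taken from existing logs and visit records. Show the three core roles at the seven sites (3 × 7 = 21 positions) and count any additional professionals separately.
3. Keep enrollment and attrition under Acceptability. Keep engagement and dose under Adoption only if labelled indirect indicators of realistic delivery.
4. State that sites were selected partly for their strong support of the program, so the Adoption result describes supportive sites.

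The cost is one table row, one sentence and a tabulation of records already planned, with no new data collection. The downside is that Adoption becomes mainly qualitative and descriptive and shares source data with Appropriateness and Feasibility. The report should say so.

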### Implementation analyses

Table 3 also provides the types of analyses that will be undertaken in the implementation evaluation. Both quantitative and qualitative methods will be employed in the evaluation, depending on the outcome being examined. Acceptability will be assessed by comparing observed rates (e.g., enrollment, eligibility, engagement, and dose) with preset targets. Many of these rates will also be used in evaluating maintenance. Reach will be assessed by reviewing baseline characteristics of the total sample and comparing these to the broader population of older adults with T2DM and MCC. A review of the records on eligible clients will also be conducted, to compare those that enroll in the study to those that do not enroll, withdraw or are lost. These records will capture demographic characteristics (e.g., age, gender, comorbidity, and site) as well as the reasons clients declined to participate, withdrew, or were lost. These analyses will enable us to assess the representativeness of the intervention group compared to those that were eligible but declined to participate, withdrew, or were lost. We will also examine the reasons for refusal and evaluate whether declines can be attributed to the nature of the program being offered.

Qualitative descriptive methods will be used to assess the content of focus groups, outreach meeting records, and other documents (e.g., log sheets documenting delivery of program components and principles used). Data from the focus groups will be digitally recorded and transcribed by an experienced transcriptionist and checked for accuracy by a RA. The data will be managed using N-Vivo 10 software. Content analysis will be used to analyze the transcripts. Two research investigators will independently review all transcripts and inductively generate a list of codes describing the content. The codes will then be grouped into themes (a higher conceptual level) and subthemes. Difference of opinion between the two investigators will be discussed until agreement is reached.

The cost analyses will involve comparing the cost of use of specific health and social services between the intervention and control groups. Because cost data are often right skewed, we anticipate using nonparametric tests (e.g., Mann-Whitney *U* test) to evaluate differences in median costs between the two groups. We will also estimate the costs of the program, and total costs of health care and social service in the two groups.

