### Participants and setting

A strategic first step for this study was the development of a partnership between researchers in the Aging, Community and Health Research Unit (ACHRU) at McMaster University (Hamilton, ON, Canada) and the University of Alberta (Edmonton, AB, Canada), program coordinators from seven community-based organizations, and seven diabetes education centers (Ontario) or primary care networks (Alberta). The study will enroll 160 participants in each of two Canadian provinces, Ontario and Alberta. Although these provinces are in the same country, they encompass diverse characteristics in terms of geography (Ontario is in the east, Alberta the west), culture, and health care system structure. In Ontario, study participants will be recruited from clients who have been recently referred for diabetes-related services to diabetes education centers (DECs). DECs are regional centers that provide ongoing diabetes education programs, counselling and follow-up sessions by registered nurses (RNs) and registered dietitians (RDs) for clients and their families. In Alberta, study participants will be recruited from clients who have been recently referred to diabetes or chronic disease management programs at three primary care networks (PCNs). PCNs are centralized resource facilities that provide equipment and health care teams to service clients from physician clinics in close proximity to one another. The Ontario and Alberta provinces were selected to compare and contrast different health care systems. The specific sites within each province were selected because they serve a large and growing older adult population, and demonstrated strong support for the program. Community partner organizations were selected and invited based on existing collaborations with the sites and/or interest in health promotion for community-dwelling older adults. The community partners were also selected based on availability and accessibility of an appropriate space to host monthly group program sessions and availability of staff members to participate in program delivery (e.g., a program coordinator for the group sessions).

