### Sample size

The sample size for the RCT was calculated to detect a minimally important difference (MID) in the primary outcome measure (PCS-12). The developers suggest that the MID for interpretation of group mean PCS-12 score differences is approximately 3.0, which corresponds to an effect size of 0.30 [56]. However, the developers also acknowledge that this MID estimate is a matter of ongoing debate. Robust research on effect sizes seen across a range of studies using a variety of quality-of-life measures has shown that the mean effect size is remarkably consistent at 0.50, or half the standard deviation [57]. This effect size is close to the one observed in our pilot study, which was 0.40 [43].

We based our estimate of the sample size on an effect size of 0.50, 5% alpha, 80% power and 20% attrition (18% was observed in our pilot study). Using these assumptions, the sample size was 80 (each) for the intervention and control groups.

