### Randomization design

After providing written, informed consent and completing the baseline questionnaires, participants will be randomly assigned to either the intervention or the control arm of the study using a 1:1 allocation ratio. Stratified permuted block randomization will be used to assign participants to the control and intervention groups. Study sites are expected to be relatively homogeneous regarding client sociodemographic and clinical characteristics and the delivery of intervention and usual care services. However, to minimize the confounding effects of possible differences among the study sites, the sites will be used as a stratum. The randomized sequence at each site will be based on assignments of blocks randomly selected from sizes of 2, 4, or 6. A biostatistician not involved in the recruitment process will generate the random number assignments for each site using SAS Version 9.3. Random number sequences will be input into a centralized web-based randomization service (REDCap) that will allocate clients to the control or intervention group at each site in accordance with the sequence.

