### Analyses

#### Analysis of participants

The data collected will be screened for accuracy, missing data, outliers, and statistical assumptions. SAS Version 9.3 will be used for all statistical analyses. All statistical tests will be performed using two-sided tests at the 0.05 significance level. For all models, the results will be expressed as effects, standard errors, 95% confidence intervals, and associated *p* values. The evaluation will be conducted in accordance with the intention-to-treat principle; therefore, imputation (using multiple imputation) will be used to address missing data and compare these results with the complete case analysis. If there are discrepancies between the multiple imputation and complete case results, we will conduct a sensitivity analysis using different multiple imputation methods (appropriate for the pattern of missingness) to see how robust the analysis is for the chosen method(s) of handling missing data [85]. This procedure will result in multiple data sets and models being run on each data set. Appropriate methods will be used to combine the results to generate pooled parameter estimates, standard errors, and confidence limits.

An analysis of baseline (*T*1) data will be performed to compare the demographic and clinical characteristics of the intervention and control groups. This analysis will confirm whether the two groups are equal on these variables. Means and standard deviations will be generated for continuous variables, and frequencies and proportions for categorical variables. The appropriate significance test (e.g., *t* test for continuous measures, chi-square for categorical) will be applied to identify any significant differences between the groups. Significant differences will be adjusted for in the outcomes analyses.

For the analyses relating to clients, *t* tests will be used to compare the changes in primary and secondary outcomes from baseline (*T*
_1_) and 6 months (*T*

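### The between-arm cost comparison is valid but leaves each client's baseline HSSUI cost unused; adjusting for it would gain precision without new data

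*Protocol article*

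**What the plan says.** Costs of health service use are part of objective 1 (clients) and objective 3 (family caregivers). The Implementation analyses section states: "The cost analyses will involve comparing the cost of use of specific health and social services between the intervention and control groups". Because costs tend to be right-skewed, it anticipates a nonparametric test, with Mann-Whitney U as the example, to compare medians between arms. It names no covariate or stratum.

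The Cost row of Table 3 is worded differently. It begins "Comparison of baseline" and sets the T1 cost against the 6-month (T2) cost, again with Mann-Whitney U. So the HSSUI is costed at both times. Its recall period is 6 months for hospital and physician use and 2 days for medication.

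Under Randomization design, "the sites will be used as a stratum". The Analysis of participants section carries site into the repeated-measures ANCOVA for the primary and secondary measures, but cost is not listed among those measures.

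**The concern.** A client's service cost in the months before randomisation may predict cost in the six months after it. Where it does, a comparison that ignores T1 cost carries variation that could be removed, so the cost contrast is less precise than the collected data allow. The article expects the program to be feasible at no additional cost and presents the cost analysis as important to policy-makers. What is at stake is power and interval width on that objective, not validity.

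**Working it through.** **Inputs from the article**
- Significance level: "All statistical tests will be performed using two-sided tests at the 0.05 significance level".
- Allocation: "using a 1:1 allocation ratio".
- Planning assumptions: "We based our estimate of the sample size on an effect size of 0.50, 5% alpha, 80% power and 20% attrition". These concern the PCS-12; no effect size or power is given for cost.
- Size: "the sample size was 80 (each) for the intervention and control groups".

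**Reproducing the stated size**
- Normal approximation: n = 2(1.960 + 0.842)² / 0.50² = 62.8, so 63 per arm; 63/0.8 = 78.75, so 79.
- t-test version: 63.8, so 64 per arm; 64/0.8 = 80.

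The stated 80 per arm reproduces, and it implies 80 × 0.8 = 64 completers per arm.

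**Assumptions, because the article gives none for cost**
- Log-normal costs with a coefficient of variation (CV) of 1.5: log-scale SD σ = √ln(1 + 1.5²) = √1.179 = 1.086.
- Cost ratio 1.5: ln 1.5 = 0.405, a standardised log-scale effect of 0.405/1.086 = 0.373.
- Log-scale T1-T2 correlation ρ from 0.2 to 0.75.

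**Hand check of the unadjusted test.** The noncentrality of a normal test on log cost is 0.373 × √(64/2) = 2.11. Mann-Whitney has relative efficiency 3/π = 0.955 here, so 2.11 × √0.955 = 2.06, and power is about Φ(2.06 − 1.96) = 54%. This agrees with the simulated value of about 53%.

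**Simulated power, 64 per arm**

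| ρ | Mann-Whitney on T2 cost | Rank ANCOVA on T1 cost |
|---|---|---|
| 0.2 | about 53% | about 54% |
| 0.4 | about 53% | about 60% |
| 0.6 | about 53% | about 70% |
| 0.75 | about 53% | about 84% |

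Type I error is about 5% for both tests.

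**Second route, by variance factor.** A baseline covariate multiplies the residual variance by 1 − ρ². Take an assumed standardised effect of 0.50 and 64 per arm, where unadjusted power is 80.7%:

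| ρ | 1 − ρ² | Power | Equivalent n per arm, 64/(1 − ρ²) |
|---|---|---|---|
| 0.2 | 0.96 | 82.3% | 67 |
| 0.3 | 0.91 | 84.3% | 70 |
| 0.5 | 0.75 | 90.4% | 85 |
| 0.7 | 0.51 | 97.7% | 125 |

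**If mean cost is modelled instead.** The raw-scale correlation is r = (exp(ρσ²) − 1)/(exp(σ²) − 1), where the denominator is 3.25 − 1 = 2.25. This gives r = 0.27, 0.46 and 0.63 at ρ = 0.4, 0.6 and 0.75. The variance reduction r² is then about 7%, 21% and 40%.

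**Site.** In a simulation with seven sites, stratified allocation and a site intraclass correlation of 0 or 0.05, adding site to the rank ANCOVA changed power by less than 1 percentage point.

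**If Table 3 means arms compared on change.** In the same seven-site simulation (standardised effect 0.50):

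| ρ | T2 cost alone | Raw change | Rank ANCOVA on T1 cost |
|---|---|---|---|
| 0.3 | 78–80% | 64–66% | 81–84% |
| 0.5 | 78–79% | 76–78% | 88–89% |
| 0.7 | 79% | 92–94% | 96–97% |

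The first two columns are Mann-Whitney tests. Raw change loses to T2 cost alone at 0.3, is slightly below it at 0.5, beats it at 0.7, and never reaches the adjusted analysis.

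**If the trial is larger.** Participants and setting says: "The study will enroll 160 participants in each of two Canadian provinces, Ontario and Alberta", whereas the abstract gives 160 across both provinces. On the larger reading there are 160 × 0.8 = 128 completers per arm. With a standardised effect of 0.35, power goes from 80.0% to 83.5%, 89.9% and 97.5% at ρ = 0.3, 0.5 and 0.7. The point holds on either reading.

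**The case against.** The strongest reply is that the article leaves the test open: it anticipates a method and offers Mann-Whitney only as an example, and covariates could be set in a fuller document. That stands as a reason not to call this an error. It does not remove the point, because the only method the article names, in the text and in Table 3, is one that cannot take a covariate.

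A second reply is that Table 3 may intend a comparison of change, which would use T1 cost. The wording allows that, and also allows arms compared at each time or T1 against T2. Raw change is still the less efficient use of T1 cost, and the row does not match the text.

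A third is that the gain rests on an unstated correlation, which the 2-day medication recall may lower. This stands: at 0.2 the gain is only 1 to 2 points.

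Three stronger readings might be inferred, and the documents do not support them:
- **That chance imbalance in baseline cost makes the planned test misleading.** At CV 1.5 the chance difference in mean baseline cost does have an SD of 1.5 × √(2/64) = 27% of the mean. But the unadjusted test keeps its 5% type I error under randomisation, and imbalance reaches T2 only in proportion to the correlation.
- **That leaving out site costs precision.** The article expects sites to be similar in clients and usual care, describes variation in usual care across the provinces, and the simulated gain is negligible.
- **That the power figures cover caregivers.** Their participation is optional and no number is stated.

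**Conclusion.** The planned cost comparison is valid but inefficient, because it does not use a T1 cost that is already collected. Under the stated assumptions, adjustment adds about 1 point of power at a correlation of 0.2, 7 at 0.4, 17 at 0.6 and 31 at 0.75, from a base of about 53%. The size cannot be narrowed further, since neither the cost SD nor the correlation is in the documents. Almost all the gain comes from T1 cost; site belongs in the model for consistency with the stratified randomisation and the clinical models. A reader should not conclude that the plan is wrong or that false positives are raised: this is an improvement available for free.

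**What to change.** In Implementation analyses, state that the main between-arm comparison models T2 cost on arm, with T1 HSSUI cost as covariate and site as a factor. Use rank ANCOVA if the rank approach is kept, or a regression of mean cost with bootstrap intervals. These answer different questions, so choose one in advance. Keep Mann-Whitney on T2 cost as a sensitivity analysis, and reword the Cost row of Table 3 to match. The same model may serve for caregiver costs where numbers allow, without borrowing the power figures above. The change costs one sentence and one table cell, and adds no data collection or participant burden.
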